### Study setting and participants

This study has been or will be conducted in six settings: Accra, Ghana (Ghana Atomic Energy Commission); Bangalore, India (St John’s Research Institute); Taguig, Philippines (Food and Nutrition Research Institute); Blantyre, Malawi (Kamuzu University of Health Science), Rabat, Morocco (National Center for Energy, Nuclear Sciences and Techniques) and Lusaka, Zambia (TROPGAN and the University of Zambia). This multicountry coordinated study design supports our capacity to capture important variation in the aetiology of stunting. For example, the relative importance of inadequate diet quality versus specific enteric pathogen exposures may vary by context (table 3). A high burden of enteric pathogen infections in early life^26^,^28^ may impact small intestinal function^29^ in a manner that may increase protein and AA requirements even though infant diets meet standard recommended protein intakes.^30^

**Table 3 T3:** Site characteristics

	Ghana*	India†	Malawi†	Morocco‡	Philippines§	Zambia†
Rural/urban	Urban	Urban	Rural	Urban	Urban	Urban
Study setting	Hospital	Hospital	Health centre	Hospital	Community	Community
Under five stunting prevalence	18%	32.3%	42%	15.5%	23.6%	35%
Under five wasting	6%	6.3%	3%	3%	5.6%	4%
Food insecurity prevalence	3%	58.1%	60%	36%	31.4%	93.4%
Minimum dietary diversity—prevalence	13%	51.6%	15%	60%	13.8%	42.4%

* Based on the Ghana demographic health surveys^55^ and statistics reported by the FAO^56^ and UNICEF.^57^

† As reported in prior studies^58^ or from unpublished data.

‡ As reported by World Bank country income classification; Human Development Index Score and Global Hunger Index severity level and by Moroccan nutrition survey (2019–2020).

§ 2023 National Nutrition Survey for stunting, wasting and food insecurity data and 2021 National Nutrition Survey for minimum dietary diversity data.

FAO, Food and Agriculture Organization.

### Eligibility criteria

Participants must meet all the inclusion and exclusion criteria to be enrolled in the study (table 4). At each site, study treatment will not begin until a participant is enrolled.

**Table 4 T4:** Inclusion and exclusion criteria

Inclusion criteria	Exclusion criteria
Of either sex	
18–36 months old	<18 months old >36 months old
Stunted (LAZ <−2) or severe stunting (LAZ <−3) (in Zambia)	Wasted (WLZ <−2) Overweight (WLZ >2)
	Moderate and severe anaemia (Hb≤99 g/L) (in Malawi)
For African sites, able and willing to undergo HIV testing	Have any underlying condition other than HIV, which in the opinion of the investigator would put the participant at undue risk of failing study completion or would interfere with analysis of study results.
Parent, caregiver or guardian able and willing to provide written informed consent	
	Have had diarrhoea (by self-report) in the preceding month
	Sibling or twin of another participating study child (two children of different families in the same household are both eligible)

Hb, haemoglobin; LAZ, length-for-age z-score; WLZ, weight-for-length z-score.

### Randomisation

Following enrolment, participants will be assigned into either the intervention or control arm of the study with equal probability. Block randomisation will be employed to ensure comparable allocation in the sequence of assignments of the participant. The randomisation sequence generation and allocation for the trial will be conducted by the coordinating team at Rutgers University using a random number generator with a fixed reproducible seed. Randomisation data will be provided to study sites using opaque, sealed envelopes.

### Study intervention

Following the baseline study assessments, each participant in the intervention group will receive a daily IAA supplement, to be mixed into the child’s usual complementary food. The crystalline IAA mix powder (containing histidine, isoleucine, leucine, lysine, methionine, phenylalanine, threonine, tryptophan and valine).

The daily dose provides ×1.5 times the daily estimated average requirement (EAR) for a healthy child. This dose was estimated as follows. First, children with EE are likely to have higher protein requirements than healthy children: although no direct data on children with EE is available, it has been estimated that protein requirements are increased by 10% in children with intestinal parasites, 20% in children convalescing from acute bacterial infections and 30% in those recovering from acute diarrhoea.^31^ Second, based on the WHO/Food and Agriculture Organization 2007 recommendations, a safe level of protein intake is set at +1.96 SD above the EAR^31^: equivalent to 1.22 times the EAR. Therefore, the study dose is 1.22 times the EAR, multiplied by 1.25 to reflect an estimated ∼25% increase in protein requirements for a child with EE, resulting in a total of 1.5 times the EAR. This IAA dose will be taken once daily by the child for 4 weeks (28 days). The study dose is calculated according to the weight of the child. The IAA supplement was prepared in a single batch and distributed to the six sites in convenient heat-sealed, moisture resistant packaging for dispensing on site. Further details of the IAA mix quality specifications, producer and quality assurance systems may be found in the supplemental materials (online supplement 2, Detailed description of intervention).

#### Intervention monitoring

The study team will directly observe up to three feedings per week (12 out of the 28 days period). The uptake on non-observed days will be based on the caregiver’s report. On each intervention monitoring day, a questionnaire will also be administered to assess child morbidity for that day and on the day prior.

#### Safety issues for intervention

There is currently no established upper limit for safe amino acid intake.^32^ However, there are some reports of adverse effects associated with high dosages (∼10–30 times higher than proposed in this study), especially with prolonged use.^33^ The doses we propose are similar to those used in multiple prior studies to promote growth and development in low birth weight or premature infants.^34^ A recent systematic review noted no increase in the incidence of adverse events in these trials.^34^

#### Outcomes and case definitions

We will collect child stool, blood, urine and breath samples, both at baseline and endline, to conduct the following tests of intestinal status and function. All outcome measures for this study are expressed as changes from baseline.

#### Primary outcomes

*LR dual-sugar test*. The LR test is the most commonly used method to assess intestinal disruption in EE, because it is posited to measure intestinal permeability.^35^ At baseline and endline, the LR test will be administered. Guardians will be asked to fast their child for 1 hour prior to the appointment. A single urine sample will be collected before the start of the study and the time noted. At the start of the test, a 9 mL of drinking water spiked with 1 g lactulose and 0.2 g rhamnose will be administered, and again a 2 mL chaser of drinking water will be used to rinse the vial. The total volume (1 mL sucrose solution+2 mL chaser+9 mL LR solution+2 mL chaser) is 14 mL. All urine passed from 30 min up to 5 hours will be collected and pooled and the total volume noted. Water or breastmilk can be freely consumed throughout the test period. Sites have chosen between a possible 3-hour or a 5-hour LR collection protocols based on local logistical considerations (ie, ease of administration in young children).

#### Secondary outcomes

*DSIT of protein digestion and absorption*. The DSIT will be administered to test the extent to which protein derived amino acids present in the test meal are released into circulation. The DSIT has previously been described elsewhere.^21 23^ In brief, complete digestion and absorption of protein derived amino acids will equate to the ratio of ^13^C amino acids in protein to ^2^H free amino acids in the meal being equal to the isotopologues ratio in plasma amino acids. Deviation from equality of amino isotopologue ratios between meal and plasma pools implies impaired gut function and reduced bioavailability of protein derived amino acids. To complete the DSIT, a single blood sample is collected from the child before the start of the study. The child will then receive a test meal designed to provide 1/3 of their daily calorie requirements as well as a dual stable isotope tracer mix of U-^13^C spirulina (10 mg/kg body weight) and ^2^H-AA mix (1.25 mg/kg body weight). The test meal is split into nine mini-meal portions. The child will first consume a three-portion priming meal followed by five portions consumed hourly to achieve a plateau in AA plasma isotopic enrichment. The ninth mini-meal portion is frozen to −80°C degrees, lyophilised, ground and stored for later analysis. Water or milk can be freely consumed throughout the test period. An additional blood sample will be collected at 5 hours after the commencement of the study in a simplified protocol based on a previous study that shows plateauing of isotopic enrichments at 5 hours.^21^

*^13^C-SBT*. The ^13^C-SBT is a breath test used to assess intestinal sucrase-isomaltase activity, which may be a proxy for alterations to intestinal function in.^2036^,^38^ A baseline breath sample is collected before giving the child a 40 mg/mL ^13^C_12_-sucrose solution, administered at a dosage of 10 µL per kg body weight (spiked in 1 mL of drinking water). This is followed by breath sample collections every 15 min for the first hour and then every 30 min for another 3 hours (a total of 4 hours). The child should consume only water or milk over the first 90 mins of the test where possible.

*Plasma biomarkers of gut function*. Plasma samples taken during the DSIT will also be used to assess *LPSBP* and iFABP, biomarkers that are elevated in EE.

*Faecal MPO and NEO*. Faecal samples will be collected to assess faecal MPO and NEO, frequently-used measures of intestinal inflammation in EE.^5^ NEO is a marker of interferon-gamma mediated activation of macrophages by T helper cell 1,^39 40^ while MPO is largely a marker of neutrophil activation.^5^

#### Additional outcomes

Questionnaires will be used to collect demographic (eg, age, sex, race) and socio-economic information using the Water, Assets, Maternal education and Income index.^41^ In addition, questionnaires will be used to assess dietary data (dietary diversity), modified to include information about the consumption of plant foods that fix CO via a C_4_ (Hatch and Slack) pathway, resulting in a greater natural abundance of ^13^C that may elevate baseline ^13^CO_2_ levels in the breath in participants.^42^

#### Additional optional outcomes

Our coordinated clinical trial design also implies that each trial team has flexibility in including additional optional outcomes, dependent on the capacity and scientific interests of the team. Optional outcomes include the following:

*Breath sampling during the DSIT*. To evaluate whether ^13^CO_2_ breath testing during the DSIT can be used as a non-invasive test of protein digestion, a priming dose of NaH^13^CO_3_ (3 µmol/kg) will be added to the DSIT meal. We will perform a correlative study of ^13^CO_2_ breath at plateau enrichment, that is, parts per million (ppm) of ^13^C post dosing minus baseline ppm ^13^CO_2_, in comparison to the DSIT result.

*^15^N test to measure dietary N bioavailability during the DSIT*. To evaluate whether the AA supplementation improves dietary nitrogen bioavailability, the DSIT 3-portion priming meal may also be extrinsically labelled with commercially affordable 98% enriched ^15^N spirulina (5 mg/kg). The ^15^N recovery will be followed in plasma and urinary metabolic pools (using the same samples collected to assay the primary and secondary study outcomes) that are known to be sensitive to amino acid absorption. Indeed, it was reported in pigs^43^ and humans^44^ that protein malabsorption induced by chronic pancreatitis was associated with a lower postprandial recovery of ^15^N in plasma protein and urinary urea.

*Glycylsarcosine (Gly-Sar) test*. Amino acids can be absorbed in small peptide form as well as free amino acids. To evaluate gut dipeptide by the transporter PepT1, Gly-Sar^45^ may be administered alongside the DSIT and/or LR tests. A single urine sample is collected before the start of the test, followed by a 1 g dose of Gly-Sar administered with 10 mL water. All urine passed up to 5 hours is collected and pooled and the total volume noted.

### Safety issues for outcome measures

This study uses a combination of common and newer tests to assess infant gut function. Some of these involve providing the infant with a small dose of tracer molecules to estimate intestinal absorption of the probe. These tests are: the dual sugar LR test of intestinal permeability,^35^ the ^13^C-SBT of intestinal sucrase activity^20 38^ and the DSIT of protein absorption.^23^ The LR test involves feeding infants a small dose of sugary solution, the ^13^C-SBT similarly involves a small dose of ^13^C-labelled sucrose solution and the DSIT involves feeding infants U-^13^C spirulina, ^2^H-AA mix and NaH^13^CO_3_ mixed into complementary foods. Stable isotopes are not radioactive and are naturally found in food sources,^46^ so the risks associated with the ^13^C-SBT and DSIT are equivalent to those of consuming the unlabelled probe. One health risk associated with these tests is that some infants may not tolerate the solution (eg, the sugary solution may cause them to vomit or spit up) or they may not like the unfamiliar taste of spirulina, a plant-based protein with a bright blue-green colour. An additional health risk of the DSIT is that it requires two 2 mL blood collections over a 5-hour period and an additional 0.5 mL for the inflammatory marker tests (LPSBP and iFABP). The two-point blood collection is currently the minimal acceptable protocol to produce interpretable data on specific amino acid absorption. The LR test requires non-invasive urine collection, the ^13^C-SBT requires non-invasive breath collection and MPO and NEO tests require faecal collection. The risk to the child is that they may be uncomfortable or not like having their urine/breath/faeces collected. Study staff will employ gentle, child-friendly methods to minimise distress.

### Biological sample collection and archiving

All biological samples will be collected, processed and preserved as per the study standard operating procedures (SOPs). Faecal samples will be collected and aliquoted into sterile, prelabelled 2 mL cryovials without additives. For blood samples, the study team will collect whole venous blood samples as per the SOPs. The sample will be centrifuged to separate plasma, and the plasma will then be aliquoted and stored at −80°C. Urine samples will be aliquoted and stored immediately at −80°C without preservative. Breath samples will be collected in white-capped, finger-tight breath collection tubes, stored at room temperature and sent to the laboratory no more than 3 months after the initial collection.

### Laboratory analysis

Laboratory analyses will be conducted either on site or at centralised laboratories, depending on the requirements of the test outcome measure. Faecal biomarkers and plasma iFABP and LPSBP will be assessed on site. Urine samples will be sent to St John’s Research Institute laboratory for L/R analysis by gas chromatography mass spectrometry (MS). Plasma samples and test meal food samples will also be sent to St John’s Research Institute or the University of Glasgow laboratory for the ^2^H/^13^C DSIT analysis by liquid chromatography MS/MS. Breath samples will be sent to St John’s Research Institute laboratory for ^13^C analysis by isotope ratio mass spectrometry (IRMS) or to the University of Glasgow. Urine (total volume to be recorded) and plasma samples from children receiving an additional dose of ^15^N spirulina will be sent to AgroParisTech to be measured by EA-IRMS.

### Data safety monitoring plan

Each trial site will appoint their own Data Safety and Monitoring Board, independent of the sponsor, according to local legal and regulatory requirements.

### Monitoring adverse events

Study participants will be monitored for any adverse events or significant changes in clinical status. If any adverse events are observed, participants will be referred for treatment. The specific protocol for referral and treatment is separately established by the local site. All adverse events will be reported to the appropriate ethics review board and study registry.

### Sample size

The sample size for this study is based on the minimum number of participants necessary to observe differences in the primary outcome variable (ΔLR) between intervention and control groups.^47 48^ Each site will contribute data from 60 children, for a total of 360 children across six sites. Assuming an intraclass correlation coefficient (ICC) of 0.1 in ΔLR ratios based on prior reports,^49^ this is sufficient to detect a standardised effect size of 0.40 or greater (a change in ΔLR equal to or greater than 0.4 SD) with an α value of 5% and 80% power. This is equivalent to changes in LR reported in response to other nutritional interventions^47 48^ and is substantially greater than previously reported effect sizes for glutamine and glycine.^50^ A sample size of 60 participants is also sufficient to detect within-site differences with a standardised effect size of 0.84 or greater (ΔLR equal to or greater than 0.84 SD). This difference is on the order of the prior reports of glutamine and glycine supplementation.^50^ Assuming a similar ICC for DSIT results, the same effect sizes (0.40 or greater for pooled analyses and 0.84 or greater for within-site analyses) would be detectable. A prior study on specific amino acid absorption in children within and without EE reported differences in mean amino acid absorption between the group equivalent to an effect size of 0.5.^51^ However, our study will be the first to use the DSIT to evaluate changes in protein digestion associated with a nutritional intervention.

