**Figure 2 F2:**
[figure not shown]
Coordinated research project design. A visual depiction of our coordinated research project design. AA, amino acid; 13C-SBT, 13C sucrose breath test; DSIT, dual stable isotope test; EE, environmental enteropathy; Gly-Sar, glycylsarcosine; iFABP, intestinal fatty acid binding protein; LPSBP, lipopolysaccharide binding protein; LR, lactulose/rhamnose test; MPO, faecal myeloperoxidase; NEO, faecal neopterin.

This is an open label study. In each trial, 18–36 months old children in the intervention arm will receive IAA supplementation for 28 days, while children in the control arm will receive only standard complementary foods for the same duration (figure 3). The study will be unblinded. Each of the six study sites will aim to recruit 60 children, half in the intervention arm and half in the control arm (see ‘Sample Size section’ for further details). Data collection began in August 2025 and is anticipated to be completed in all sites by June 2026. Site-specific start dates and enrolment status are reported in online supplement 1 (Standard Protocol Items: Recommendations for Interventional Trials (SPIRIT) guidelines for each site).

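### The stated detectable effects (0.40 SD pooled, 0.84 SD within site) do not follow from the stated inputs, and the pooled figure is not tied to the planned logistic analysis

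*Protocol article*

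**What the plan says.** The Sample size section fixes the numbers: "Each site will contribute data from 60 children, for a total of 360 children across six sites". It continues "Assuming an intraclass correlation coefficient (ICC) of 0.1 in ΔLR ratios based on prior reports" and concludes that "this is sufficient to detect a standardised effect size of 0.40 or greater", "with an α value of 5% and 80% power". The effect is expressed in SD of ΔLR. For a single site it says: "A sample size of 60 participants is also sufficient to detect within-site differences with a standardised effect size of 0.84 or greater". That sentence gives no power level of its own. Both figures are then carried over to the DSIT.

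The design behind these figures is clear. In the Overview of the trial design: "Each of the six study sites will aim to recruit 60 children, half in the intervention arm and half in the control arm". In Randomisation: "participants will be assigned into either the intervention or control arm of the study with equal probability". Children are therefore the unit of randomisation, and both arms are present in every site.

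The Statistical analysis section plans a Wilcoxon rank-sum test of change within each site. For LR across sites it plans a logistic regression of being above or below an EE cut-off on study arm.

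**The concern.** The two detectable effects justify the sample size and tell a reader what a null result would exclude. The section gives inputs and outputs side by side, so the outputs can be checked, and they do not match.

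The pooled figure has two faults. It is not the 80%-power threshold for the quantity it names, a difference in mean ΔLR. That quantity is also not what the combined LR analysis estimates. A reader therefore cannot tell whether 0.40 SD describes a mean comparison (where it is too large), the logistic comparison (where it is about the right size, but on another scale and with unstated inputs), or a calculation with some unstated allowance.

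The role of the ICC is also unclear. It is presented as an input that limits the detectable effect, but with individual randomisation inside each site a between-site ICC does not inflate the contrast between arms.

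**Working it through.** **Inputs.** 60 children per site, six sites, 360 in total, ICC 0.1, alpha 5%, power 80% (Sample size); half per arm in each site, so 30 v 30 within a site and 180 v 180 pooled (Overview of the trial design). Sidedness is not stated; two-sided is assumed.

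**Formula.** Detectable effect in SD = (z for alpha + z for power) × √(2/n per arm). At two-sided 5% and 80% power the multiplier is 1.960 + 0.842 = 2.802.

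**Pooled, attempt to reproduce 0.40.**
- Site ignored: 2.802 × √(2/180) = 2.802 × 0.1054 = 0.295 (noncentral t: 0.296).
- Site removed in the analysis: with 10% of the variance between sites, 0.295 × √0.9 = 0.280.
- ICC as a cluster design effect, site-by-arm groups of 30: 1 + 29 × 0.1 = 3.9; 0.295 × √3.9 = 0.58.
- ICC as a cluster design effect, sites of 60: 1 + 59 × 0.1 = 6.9; 0.295 × √6.9 = 0.78.
- Design effect needed to reach 0.40: (0.40/0.2953)² = 1.83, which an ICC of 0.1 does not give with clusters of 30 or 60.
- 90% power instead of 80%: 3.242 × 0.1054 = 0.342. One-sided 5% at 80% power: 0.262.

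Power at 0.40 SD is Φ(0.40/0.1054 − 1.960) = Φ(1.835) = 96.7% with site ignored, and Φ(0.40/0.100 − 1.960) = Φ(2.04) = 97.9% with site removed. For 80% power at 0.40 SD, 2 × 2.802²/0.40² = 98.1, so 99 per arm would suffice.

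**Within site, attempt to reproduce 0.84.**
- Normal formula: 2.802 × √(2/30) = 2.802 × 0.2582 = 0.723.
- t test (noncentral t): 0.736.
- Wilcoxon, normal data (relative efficiency 0.955): 0.736/√0.955 = 0.753.
- 90% power: 3.242 × 0.2582 = 0.837 (normal formula) or 0.851 (t).

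Power at 0.84 SD is 90.2% (normal formula) or 89.2% (t). At 80% power, 23 per arm would suffice. The figure 0.84 therefore fits 90% power with exactly 30 per arm, but the same power level gives 0.342 pooled, so this reading does not explain both figures.

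**Pooled, on the analysis planned.** The proportion of controls above the EE cut-off is not in the article, so a range is assumed. Take LR on a normal scale, let p be the control proportion above the cut-off, and let supplementation lower LR by d SD. The intervention proportion is then 1 − Φ(Φ⁻¹(1 − p) + d). Solving a two-proportion comparison of 180 v 180 for 80% power, with site ignored, gives:

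| Controls above cut-off (assumed) | Detectable shift, SD |
|---|---|
| 25% | 0.43 |
| 50% | 0.37 |
| 60% | 0.37 |
| 75% | 0.39 |
| 80% | 0.40 |
| 90% | 0.46 |

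Check at p = 50%: d = 0.373 gives 35.5% above the cut-off in the intervention arm, a difference of 14.5 points. The null standard error is 0.0521 and the alternative one 0.0516; (0.145 − 1.960 × 0.0521)/0.0516 ≈ 0.83, which is 80% power. Across the same range, power is about 43-62% at 0.30 SD and 67-86% at 0.40 SD. The SD here is that of the LR value that is dichotomised, not of ΔLR.

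**The case against.** The strongest reply is that both statements are literally true for a mean difference. The design can detect 0.40 and 0.84 SD or more, with power above 80%, so nothing is put at risk and recruitment does not change. This stands, and it sets the limit of the point: the figures are misstated as thresholds, but conservatively.

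A second reply is that 0.40 may reflect the logistic analysis or a treatment-by-site variance. The logistic range above includes 0.40. A treatment-by-site variance of about 0.025, with a t reference on 5 degrees of freedom, gives 0.415. This shows that 0.40 can be approached, but only through inputs the section does not name; it names ΔLR in SD units and an ICC. It does stop anyone from offering 0.28-0.30 as the sensitivity of the planned pooled test.

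A third reply concerns 0.84. Its sentence states no power, and the figure fits 90% power, or 80% power with about 20% loss plus the Wilcoxon efficiency (0.845). This stands in part: a missing label is as likely as an arithmetic error. Also, the 0.75 quoted for the Wilcoxon test assumes normal data, while the article says LR ratios generally are not normal.

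A reader might also object that no loss of paired tests is allowed for. A condensed article may leave that to the full protocol or site documents, so it is not counted here.

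**Conclusion.** The point holds in a limited form. From the stated inputs, and for a comparison of mean ΔLR, the 80%-power thresholds are 0.28-0.30 SD pooled and about 0.74-0.75 SD within site, against the stated 0.40 and 0.84. The stated values have about 97-98% and 89-90% power on that analysis. These results assume two-sided testing, 30 evaluable children per arm per site and no treatment-by-site variance.

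Two stronger readings are tempting and not supported. A reader might infer that the trial is underpowered for 0.40 because site clustering was mishandled; individual randomisation within sites rules this out for the mean comparison. A reader might instead infer that pooled effects of 0.30-0.40 SD are comfortably within reach. That is so for a continuous site-stratified analysis of ΔLR, but the combined LR analysis described is logistic, and its detectable shift is roughly 0.37-0.46 SD under the assumed 25-90% of controls above the cut-off.

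**What to change.** In the Sample size section, restate both figures with sidedness, power level and how the ICC enters the calculation, without a cluster design effect for the arm contrast.

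- **Pooled:** give 0.28-0.30 SD only if the pooled analysis is a site-stratified continuous analysis of ΔLR. Otherwise give a figure for the logistic model at a stated proportion above the cut-off.
- **Within site:** give about 0.74-0.75 SD at 80% power, or keep 0.84 and label it as about 90% power if that was intended.
- **DSIT:** revise the sentence that carries the figures over. Table 2 shows no DSIT in Zambia, so a pooled mean comparison rests on 150 v 150: 2.802 × √(2/150) = 0.32, or 0.31 with site variance removed, again taking the ICC as 0.1.

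The cost is text and arithmetic only; no more children are needed.

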**Figure 3 F3:**
[figure not shown]
Study flow chart. This figure shows the complete list of primary (LR) and secondary (DSIT, 13C-SBT, AAT, MPO, LPSBP and iFABP) biomarkers planned across the trials. Not all trials will administer all outcome measures. AA, amino acid; AAT, alpha-1 antitrypsin; 13C-SBT, 13C sucrose breath test; DSIT, dual stable isotope test; iFABP, intestinal fatty acid binding protein; LAZ, length-for-age z-score; LPSBP, lipopolysaccharide binding protein; LR, lactulose/rhamnose; mo, month old; MPO, faecal myeloperoxidase.

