### Ethics declaration

**Figure 4 F4:**
[figure not shown]
Protocol timeline. This figure shows the complete list of primary (LR) and secondary (DSIT, 13C-SBT, AAT, MPO, LPSBP and iFABP) biomarkers planned across the trials. Not all trials will administer all outcome measures. AAT, alpha-1 antitrypsin; 13C-SBT, 13C sucrose breath test; DSIT, dual stable isotope test; iFABP, intestinal fatty acid binding protein; LPSBP, lipopolysaccharide binding protein; LR, lactulose/rhamnose; MPO, faecal myeloperoxidase.

**Table 1 T1:** A representative total dose of the IAA supplement in milligrams per day, calculated for a 24-month-old child

IAA	Dose
Gly	232.1 mg/day
His	252 mg/day
Ile	453.6 mg/day
Leu	907.2 mg/day
Lys	739.2 mg/day
Met	246.3 mg/day
Cys	123.1 mg/day
Phe	336.0 mg/day
Tyr	336.0 mg/day
Thr	403.2 mg/day
Trp	100.8 mg/day
Val	604.8 mg/day
Total	4734.5 mg/day

Gly is added to support intestinal glutathione synthesis.^54^ The Gly dose is calculated as 63% of AA intake using whole egg protein as a reference.

AA, amino acid; Cys, cysteine; Gly, glycine; His, histidine; IAA, indispensable amino acid; Ile, isoleucine; Leu, leucine; Lys, lysine; Met, methionine; Phe, phenylalanine; Thr, threonine; Trp, tryptophan; Tyr, tyrosine; Val, valine.

**Table 2 T2:** Planned outcome measures in each site

	Ghana	India	Malawi	Morocco	Philippines	Zambia
LR	5-hour	5-hour	5-hour	3-hour	5-hour	3-hour
DSIT	Yes	Yes	Yes	Yes	Yes	No
13C-SBT	Yes	Yes	Yes	Yes	Yes	No
Faecal MPO and NEO	Yes	Yes	Yes	Yes	Yes	Yes
LPSBP and iFABP	Yes	Yes	Yes	Yes	Yes	Yes

13C-SBT, 13C sucrose breath test; DSIT, dual stable isotope test; iFABP, intestinal fatty acid binding protein; LPSBP, lipopolysaccharide binding protein; LR, lactulose/rhamnose; MPO, myeloperoxidase; NEO, neopterin.

Ethical approval for the study has been obtained from the Ethical Review Board overseeing research at each site. The research protocol follows ‘the Standard Protocol Items: Recommendations for Interventional Trials (SPIRIT)’.^25^

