For all statistical analysis, p values <0.05 will be considered statistically significant and intention-to-treat analyses will be applied. Both our primary and secondary outcomes will be analysed as change from baseline to endline. Because LR ratios are generally not normally distributed, we will use the non-parametric Wilcoxon rank-sum test to compare the supplementation and control groups within each site. For combined analyses we will use logistic regression models (outcome: LR ratio above vs below EE cut-off, exposure: intervention or control group). For all secondary outcomes, we will similarly use the non-parametric Wilcoxon rank-sum test to compare the supplementation and control groups within each site. For combined analyses we will use linear regression models or logistic regression models based on appropriate cut-off values, including a random effect to account for clustering by site.

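### The pooled DSIT analysis cannot have the same detectable effect as LR, because DSIT is not done in Zambia and at most 300 of the 360 children contribute

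*Protocol article*

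**What the plan says.** The Sample size section of the Protocol article fixes the planned numbers: "Each site will contribute data from 60 children, for a total of 360 children across six sites". From these, with an ICC of 0.1 for the change in LR, it gives a pooled detectable effect of 0.40 SD "with an α value of 5% and 80% power". It adds a within-site figure of 0.84 SD for 60 children.

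The section then turns to DSIT. On the single condition that the ICC is similar, it says that "the same effect sizes (0.40 or greater for pooled analyses and 0.84 or greater for within-site analyses) would be detectable". It does not mention how many sites or children will have DSIT data.

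That information is in Table 2 ("Planned outcome measures in each site"). LR is planned at all six sites. DSIT is planned in Ghana, India, Malawi, Morocco and the Philippines, and is marked as not done in Zambia. The captions to Figures 3 and 4 make the general point: "Not all trials will administer all outcome measures".

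**The concern.** The DSIT statement carries over a figure derived for six sites and 360 children to an analysis that can have at most five sites and 5 x 60 = 300 children. A similar ICC is not enough to justify this, because the sample size and the number of sites both fall by one sixth.

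The stated sensitivity matters for how the result will be read. The article presents this trial as the first to use DSIT to evaluate a nutritional intervention, and its Discussion counts DSIT among the direct measures of gut function. If the pooled DSIT result is null, readers will judge it against the detectable effect printed here, which was not worked out for the children who will have the test.

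**Working it through.** **Inputs**
- Alpha 5% and power 80%: Sample size section. Sidedness is not stated there. Two-sided is assumed, in line with the threshold under Statistical analysis, "p values <0.05 will be considered statistically significant".
- Allocation 1:1 within each site: "Each of the six study sites will aim to recruit 60 children, half in the intervention arm and half in the control arm" (Overview of the trial design).
- Unit of randomisation, the child: "participants will be assigned into either the intervention or control arm of the study with equal probability" (Randomisation).
- ICC 0.1 for LR, and similar for DSIT: Sample size section.
- Sites with LR: 6, so N = 360 and 180 per arm. Sites with DSIT: 5 (Table 2), so N = 300 and 150 per arm.

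**Step 1. Try to reproduce the 0.40 SD at N = 360.**
Detectable effect = (1.960 + 0.842) x sqrt(2V/n per arm), with V the variance in SD units.
- V = 1: 2.802 x sqrt(2/180) = 0.295 SD.
- V = 1 - 0.1 = 0.9 (between-site variance removed, because arms are compared within sites): 0.280 SD.
- Cluster design effect 1 + 59 x 0.1 = 6.9: 0.78 SD. With clusters of 30, 1 + 29 x 0.1 = 3.9: 0.58 SD.

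None of these gives 0.40. That figure implies a variance inflation of (0.40/0.295)^2, about 1.83, which the article does not explain. The next step therefore should not depend on knowing the formula.

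**Step 2. Ratio of the DSIT limit to the LR limit.**
With equal sites of 60 and the same ICC, the variance of the pooled difference is proportional to 1/(number of sites). The ratio of detectable effects is sqrt(6/5) = sqrt(360/300) = 1.095. Checks:

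| Basis | Six sites, N = 360 | Five sites, N = 300 | Ratio |
|---|---|---|---|
| Individual randomisation, V = 1 | 0.295 | 0.323 | 1.095 |
| Individual randomisation, V = 0.9 | 0.280 | 0.307 | 1.095 |
| Cluster design effect 6.9 | 0.776 | 0.850 | 1.095 |
| Treatment-by-site variance 0.05 (assumed) | 0.385 | 0.422 | 1.095 |

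The last row uses variance (2/n)(1 - 0.05) + 0.05/k for k sites, with normal quantiles.

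**Step 3. Size on the plan's own scale.**
Take 0.40 SD as the exact 80%-power limit at 360 and keep whatever inflation it contains.
- DSIT limit: 0.40 x 1.095 = 0.438, about 0.44 SD.
- Power at 0.40 SD: Phi(2.802 x sqrt(300/360) - 1.960) = Phi(0.598), about 72%.

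**Step 4. Size under simple individual randomisation within sites (V = 1).**
- DSIT limit: 2.802 x sqrt(2/150) = 0.323 SD.
- Power at 0.40 SD: Phi(0.40/sqrt(2/150) - 1.960) = Phi(1.504), about 93%. With an assumed 20% dropout it is about 87%.
- Children needed for 80% power at 0.40 SD: 198 in total, so a loss of up to 1 - 198/300 = 34% would be tolerable.

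**The case against.** The strongest reply is that the sentence claims only that effects of 0.40 SD or more are detectable, and that this may well be true with 300 children. Children are randomised individually within sites. On that basis 300 children detect 0.40 SD with about 93% power, and 198 would be enough for 80%. This stands. A reader might infer from the missing site that 0.40 SD is out of reach for DSIT, but the document does not establish that.

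A reader might also take 0.44 SD and 72% power as the true position. They follow only if 0.40 SD is the exact limit at 360, and that figure does not reproduce from the stated inputs. If a full cluster design effect applied, 0.40 SD would already fail with all six sites, and Zambia would not be the cause.

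Three further limits on the point are fair. The 0.84 SD within-site figure is untouched, because each of the five DSIT sites still plans 60 children. The 13C-SBT is also not done in Zambia, but the article states no detectable effect for it, so there is no figure to correct. The 0.5 SD cited for DSIT is described openly as a contrast between children with and without EE; it is not offered as a treatment effect and is no error.

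It can also be said that Table 2 and the figure captions disclose the missing site. They do, but they do not correct the numerical statement in the Sample size section, which still equates an analysis of 300 with one of 360.

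**Conclusion.** The point holds as an inconsistency between the Sample size section and Table 2. Given the same ICC, alpha, power and site size, the pooled DSIT limit is about 10% larger than the LR limit, and this ratio does not depend on which of the formulas in the table lies behind 0.40 SD.

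The absolute size does depend on that undisclosed basis. It is about 0.44 against 0.40 SD if the plan's figure is taken as the 80%-power limit, or about 0.32 against 0.295 SD for individual randomisation with no extra variance. Both pairs assume a two-sided 5% test, 60 children at every contributing site and no dropout.

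The consequence is modest. DSIT is a secondary outcome, and LR is planned at all six sites, so the sample size and the power for the primary outcome are unchanged. What changes is the yardstick for a null pooled DSIT result.

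**What to change.** In the Sample size section, state that the pooled DSIT analysis uses five sites (n=300). Replace the claim of identical effect sizes with DSIT's own pooled detectable effect, computed on the same basis as the LR figure, and name that basis. If the basis of 0.40 SD is kept, the DSIT figure is 0.44 SD. If both are recalculated for individual randomisation within sites, the figures are about 0.32 SD for DSIT and 0.295 SD for LR (0.31 and 0.28 with the between-site variance removed). The within-site figure is no part of this correction.

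The cost is one sentence. Recruitment, conduct and analysis do not change. The printed DSIT figure becomes less favourable than 0.40 SD on the first basis and more favourable on the second.
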